### Statistical analysis

The three groups will be compared at baseline on outcome measures and demographic information. Data will be reported as mean (SD) on continuous variables, (primary and secondary outcomes), and as percentage (number) for categorical data (demographic data, change in use of sound enrichment, medication, naps, caffeine, alcohol). A logistic model will be used to assess predictors of missing data and to examine all baseline characteristics and demographic variables.

The primary hypothesis to be tested is that CBTi will lead to a significantly greater reduction in insomnia in patients with tinnitus than usual care (ABC) from pre- to post-treatment and at follow-up, based on the primary outcomes of total ISI and 2-week average of SE and TST from a daily diary.

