### Research aims and hypotheses

#### Primary objective

The primary objective is to assess the relative efficacy of CBTi compared with ABC for tinnitus-related insomnia from pre- to post-treatment and at 1- and 6-month follow-up time points.

Hypothesis 1A: CBTi will lead to a significantly greater reduction in insomnia than ABC from pre- to post-treatment and at follow-up, as indicated by mean changes on the Insomnia Severity Index (ISI).

Hypothesis 1B: CBTi will lead to a significantly greater reduction in insomnia than ABC from pre- to post-treatment and at follow-up, as indicated by mean changes on SE and TST, measured by a 2-week daily sleep diary.

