### Outcome measures

The primary outcome will be reduction of insomnia (ISI) and improvement in subjective sleep (diary) from 3 to 10 weeks, 14 weeks and 34 weeks post-randomisation. Daily sleep diaries will be completed by participants at home; questionnaire data will be completed independently in the treatment session and collected by the trial therapists.

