### Sample size

We calculated the sample size required to test the primary hypothesis on the basis of a recent meta-analysis of 14 randomised controlled trials comparing CBTi with control groups in the treatment of primary insomnia [22]. Here, between-group comparisons reported effect sizes on subjective sleep variables (Cohen’s *d*) as ranging from medium (*d* = 0.44) to large (*d* = 1.09) across a range of control groups (including no intervention, placebo control, waiting list, treatment as usual and information controls). Similarly, medium to large effect sizes were seen on self-rating measures. When looking at treating insomnia in the context of a chronic health condition such as pain, similar moderate to large effect sizes are reported [27]. These findings have led us to base a power analysis on an assumed effect size of 0.8.

Estimation of potential loss to follow-up was set at 10%, based on rates reported by Okajima et al. [22], as ranging from 0% to 33% and as 8% from a clinical evaluation of CBTi within a tinnitus clinic [31]. We assumed a cluster design with six patients per group, and we assumed a within-group correlation of 7%, estimated from a previous study [31]. Correlation between measures was estimated as 25% on the basis of a small pilot study. It is likely that the true correlation will be higher, so this estimate has a conservative effect on required sample size. Assuming a significance level of 5% and 80% power, the number of participants needed to detect a statistically significant difference between the CBTi and ABC groups on the primary measures of interest was 34 per group (102 across all three groups).

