### Primary outcome analysis

The ISI and sleep diary data will be analysed using linear mixed models, accounting for repeated measures on participants and the cluster structure of the trial. Post hoc comparisons of independent groups will allow multiple comparisons by using adjusted *P* values. We will also conduct an analysis to indicate the number needed to treat based on reliable change in the ISI.

Analysis will be based on modified intention to treat (excluding those who contribute no data). For data missing at random, multiple imputation will be used. To minimise missing data, the research assistant will follow up on missing data after questionnaire completion.

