### Secondary outcome analysis

As for the primary analysis, a linear mixed model will be used to investigate differences in outcome between the three groups at additional time points (1-month and 6-month follow-up) and on all secondary outcome measures described above. In addition, correlational analyses will be used as a quality control to check for the level of association between actigraphy and sleep diary data, including TST, TWT, SOL and SE.

Regression analyses will be conducted to assess whether changes in the primary outcome measure (ISI, TST, SE) are associated with changes in sleep beliefs (DBAS-16) score.

Satisfaction will be assessed via a single three-group analysis of variance on treatment usefulness and relevance. Written responses will be analysed using thematic analysis. Treatment adherence will be assessed on the basis of attendance rates. Categorical outcomes, including adverse events and non-adherence, will be recorded, reported and compared with Fisher’s exact test.

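### Three primary outcomes have no success rule, the status of the follow-up visits is contradictory, and the only multiplicity adjustment is placed on the arms

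*Protocol article*

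**What the plan says.** All references are to the Protocol article.

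- **Primary objective:** "The primary objective is to assess the relative efficacy of CBTi compared with ABC for tinnitus-related insomnia", assessed "from pre- to post-treatment and at 1- and 6-month follow-up time points". Hypothesis 1A uses the ISI; hypothesis 1B uses diary SE and TST.
- **Statistical analysis:** the primary hypothesis is "based on the primary outcomes of total ISI and 2-week average of SE and TST from a daily diary".
- **Outcome measures:** the primary outcome is change "from 3 to 10 weeks, 14 weeks and 34 weeks post-randomisation".
- **Secondary outcome analysis:** the mixed model is used here for "differences in outcome between the three groups at additional time points (1-month and 6-month follow-up"), so the same two follow-ups appear as secondary.
- **Primary outcome analysis:** "Post hoc comparisons of independent groups will allow multiple comparisons by using adjusted" P values. No method is named. This is the only statement on multiplicity.
- **Sample size:** "Assuming a significance level of 5% and 80% power", 34 per group are needed for CBTi versus ABC. No allowance is made for any adjustment.
- **Secondary objectives:** CBTi versus SSG and ABC versus SSG are secondary hypotheses (2B, 2C).

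**The concern.** Three outcomes carry the primary label, and depending on the section they do so at one visit or at three. The primary CBTi-ABC family therefore holds either three or nine contrasts, and nothing says which result decides the trial. The one stated adjustment works along a different dimension, the arms. There the article already has a single planned contrast, and that contrast was sized at an unadjusted 5%.

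The stake is what the trial may claim. If any success will do, the false-positive rate exceeds the stated 5%. If all must succeed, the stated 80% power does not apply. If the arm adjustment reaches the planned contrast, that contrast is tested at a stricter level than the one it was sized for. The stated 5% and 80% hold for one test of one outcome at one visit, and the article does not identify that test.

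**Working it through.** **1. Inputs (Sample size section).** d = 0.8; 5% level (two-sided assumed, as the article does not say); 80% power; six patients per group; within-group correlation 0.07; correlation between measures 0.25; 10% loss; 34 per arm.

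**2. Reproducing the 34.**
- Basic n per arm = 2 × ((1.960 + 0.842)/0.8)² = 24.53.
- Design effect = 1 + 5 × 0.07 = 1.35.
- Baseline-adjustment factor = 1 - 0.25² = 0.9375.
- 24.53 × 1.35 × 0.9375 = 31.04. Dividing by 0.9 for loss gives 34.5; multiplying by 1.1 instead gives 34.15.

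This is close to the stated 34, using one test at the full 5%.

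**3. If any one success counts: chance of at least one false positive, each test at 5%.** For independent tests, three give 1 - 0.95³ = 14.3% and nine give 1 - 0.95⁹ = 37.0%. Correlated test statistics were simulated (400,000 draws). The correlations between outcomes and between visits are assumptions, because the article gives only 0.25 between measures.

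| Assumed correlation (outcomes; visits) | 3 outcomes, 1 visit | 3 outcomes, 3 visits |
|---|---|---|
| 0; 0 | 14.3% | 37.0% |
| 0.25; 0.25 | 13.8% | 35.0% |
| 0.5; 0.5 | 12.5% | 29.4% |
| 0.7; 0.7 | 11.0% | 22.8% |

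Counting only errors that favour CBTi, independence gives 1 - 0.975³ = 7.3% and 1 - 0.975⁹ = 20.4%. At correlation 0.7 the figures are 5.5% and 11.4%. The nominal rate for comparison is 2.5%.

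**4. If all three outcomes must succeed at one visit.** There is no inflation. With 80% power for each outcome, joint power is 0.8³ = 51% under independence, and by simulation 56%, 61% and 66% at correlations 0.25, 0.5 and 0.7.

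**5. If the arm adjustment also covers CBTi versus ABC.**
- Patients after loss: 34 × 0.9 = 30.6 per arm.
- Effective n = 30.6/1.35/0.9375 = 24.18.
- Expected test statistic = 0.8 × √(24.18/2) = 2.782.
- Power is Φ(2.782 - critical value), or its t-based counterpart.

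| Level for CBTi-ABC | Critical value | Power, normal | Power, t-based |
|---|---|---|---|
| 0.05, unadjusted | 1.960 | 79% | 78% |
| Tukey, three arms (0.0191) | 2.344 | 67% | 64% |
| Bonferroni, three pairs (0.0167) | 2.394 | 65% | 62% |

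With a correlation of 0.5 in place of 0.25, effective n is 30.6/1.35/0.75 = 30.22. Bonferroni power is then 76% (normal) or 74% (t-based).

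**6. Keeping all three outcomes at 0.0167 each.** The formula in step 2 with this level gives 45.5 to 46.0 per arm, so 46 to 47 after rounding up, against 34 to 35 at 5%.

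**The case against.** The strongest reply is that the article never says one success is enough. Its wording joins the outcomes and the time points with 'and', which fits an all-must-succeed reading with no inflation. That stands. A reader might infer that the trial has a 23-37% false-positive rate; the text does not support this, since the rate depends on an unstated rule. It is also an upper range: on the Secondary outcome analysis section's reading the family is three tests, and errors against CBTi could not meet a directional hypothesis.

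A reader might likewise infer that the planned contrast is certain to lose power. The adjustment is described for post hoc comparisons, and CBTi versus ABC is planned in advance, so it may be exempt; but the article describes no separate test for it. The loss also depends on the unnamed method and on the 0.25 correlation, which the Sample size section itself expects to be too low.

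A third inference is that SE and TST will diverge because CBTi restricts time in bed. The article reports no such divergence, and the point does not depend on it.

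Finally, the choice of adjustment method can be left to an analysis plan. True, and its absence is not the criticism. The article itself names three unranked primaries, gives two incompatible statuses to the follow-ups, and directs its adjustment at the arms. A later plan could not resolve the conflict over visits without changing what this article calls primary.

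**Conclusion.** The point holds in conditional form. What the text fixes badly is certain: there are three primary outcomes with no decision rule, the sections conflict on weeks 14 and 34, and the stated adjustment covers neither outcomes nor visits.

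The size depends on how the gap is filled:

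- **Any success counts:** about 11-14% two-sided error for three outcomes at one visit, and up to about 23-37% if all three visits are primary. Counting only errors in favour of CBTi, the figures are about 5-7% and 11-20%.
- **All three outcomes must succeed:** error is controlled, with joint power of about 51-66% at one visit.
- **Arm adjustment applied to CBTi-ABC:** power of about 62-67% instead of about 79% at a correlation of 0.25, or about 74-76% under Bonferroni at 0.5.

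These figures rest on two-sided testing, on assumed correlations between outcomes and visits, and on the Sample size section's own effect, clustering and loss. Under none of the three do the stated 5% and 80% both hold as the article presents them.

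**What to change.** Before unblinding:

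1. Reconcile the Secondary outcome analysis section with the Primary objective, Outcome measures and Statistical analysis sections on which visit or visits are primary. If more than one is, the rule in step 3 must cover visits as well as outcomes.
2. State that CBTi versus ABC is a planned contrast tested at two-sided 5%, outside the post hoc arm adjustment.
3. Control error across ISI, SE and TST. A fixed sequence starting with ISI leaves the full 5% and about 79% power with ISI. Holm across the three treats them equally, but its first step is at 0.0167, where power for a single outcome is about 65%.
4. Restate the power in the Sample size section for the rule chosen.

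Making ISI at week 10 the sole primary test is one way to do this, not the only one; the Rationale section asks for at least six months of follow-up, which is a reason to weigh how week 34 is placed.

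No new patients or data are needed if the sequence is used. The cost is that SE, TST and any later visits are tested only in sequence or at a stricter level. The change is also more than wording: recruitment was already complete when the article was proofed, and the Ethics and dissemination section requires protocol modifications to be notified to the ethics committee, participants, registry and the two institutions.

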### Primary outcome analysis

The ISI and sleep diary data will be analysed using linear mixed models, accounting for repeated measures on participants and the cluster structure of the trial. Post hoc comparisons of independent groups will allow multiple comparisons by using adjusted *P* values. We will also conduct an analysis to indicate the number needed to treat based on reliable change in the ISI.

Analysis will be based on modified intention to treat (excluding those who contribute no data). For data missing at random, multiple imputation will be used. To minimise missing data, the research assistant will follow up on missing data after questionnaire completion.

### Secondary outcome analysis

As for the primary analysis, a linear mixed model will be used to investigate differences in outcome between the three groups at additional time points (1-month and 6-month follow-up) and on all secondary outcome measures described above. In addition, correlational analyses will be used as a quality control to check for the level of association between actigraphy and sleep diary data, including TST, TWT, SOL and SE.

Regression analyses will be conducted to assess whether changes in the primary outcome measure (ISI, TST, SE) are associated with changes in sleep beliefs (DBAS-16) score.

Satisfaction will be assessed via a single three-group analysis of variance on treatment usefulness and relevance. Written responses will be analysed using thematic analysis. Treatment adherence will be assessed on the basis of attendance rates. Categorical outcomes, including adverse events and non-adherence, will be recorded, reported and compared with Fisher’s exact test.

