#### Secondary objectives

Hypothesis 2A: A greater proportion of patients receiving CBTi will show a reliable clinical change in insomnia (> 6-point reduction on the ISI) compared with ABC and SSG.

Hypothesis 2B: CBTi will lead to a significantly greater reduction in insomnia than SSG from pre- to post-treatment and at follow-up, as indicated by mean changes on the ISI, SE and TST.

Hypothesis 2C: ABC will lead to a significantly greater reduction in insomnia than SSG from pre- to post-treatment and at follow-up, as indicated by mean changes on the ISI, SE and TST.

Hypothesis 2D: Compared with both ABC and SSG, CBTi will lead to significantly greater mean changes in measures of tinnitus-related distress, tinnitus catastrophising, psychological distress, anxiety, depression, quality of life and functioning from pre- to post-treatment and at follow-up.

Hypothesis 2E: A greater proportion of patients receiving CBTi will show a reliable change on the measure of tinnitus distress (> 11 points on the Tinnitus Questionnaire) compared with ABC and SSG.

Hypothesis 2F: Participants receiving CBTi will show a greater reduction in dysfunctional beliefs about sleep than those receiving ABC or SSG, and this reduction will be associated with greater improvements in insomnia.

Hypothesis 2G: There will be no significant differences between the three groups in terms of changes in subjective tinnitus loudness after treatment.

The study will monitor safety (incidence of adverse reactions), acceptability and patient satisfaction with each treatment. Adverse events will be solicited in the feedback form and may arise spontaneously. If reported, adverse events will be recorded and included in the final report. Participants will be offered psychological support outside of the trial, or the general practitioner (GP) will be contacted as appropriate.

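### Satisfaction (ANOVA) and categorical outcomes (Fisher's exact test) are assigned tests that ignore the therapy-group clustering for which the trial was sized; the effect is material for the ANOVA and for a three-arm Fisher test, small for pairwise Fisher

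*Protocol article*

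**What the plan says.** Under Randomisation and blinding, treatment runs in cohorts, each with one therapy group per arm in parallel and about six patients per group. The Sample size section builds this in: "We assumed a cluster design with six patients per group", and "we assumed a within-group correlation of 7%, estimated from a previous study". Primary outcome analysis specifies linear mixed models that take account of the repeated measures and the clustering. Secondary outcome analysis applies the same kind of model to the secondary measures, which the Outcome measures section treats as continuous.

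The same section then names two further tests. For satisfaction: "Satisfaction will be assessed via a single three-group analysis of variance on treatment usefulness and relevance". For the rest: "Categorical outcomes, including adverse events and non-adherence, will be recorded, reported and compared with" Fisher's exact test. No cluster term or adjustment is given for either.

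Hypothesis 2A concerns a proportion: "A greater proportion of patients receiving CBTi will show a reliable clinical change in insomnia" than with either comparator. Hypothesis 2E is the same for the Tinnitus Questionnaire. Primary outcome analysis adds a number needed to treat based on ISI reliable change and names no method for it.

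**The concern.** A one-way ANOVA and Fisher's exact test both assume that participants are independent. The protocol's own design assumption is that members of a therapy group are not. Where outcomes are positively correlated within groups, an analysis that ignores this understates the variance of the arm comparison, and a nominal 5% test may reject too often.

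This is more than a detail left for the analysis plan. The protocol names the tests, and they conflict with the clustering premise used for sizing and for the primary model. At stake are the satisfaction comparison and, if the Fisher sentence is read as worded, two pre-specified secondary hypotheses. The number needed to treat rests on the same ISI responder outcome.

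**Working it through.** **Inputs from the Sample size section.** "Assuming a significance level of 5% and 80% power" (two-sided assumed, as sidedness is not stated); effect size d = 0.8; six per therapy group; within-group correlation 0.07; correlation between measures 0.25; 10% loss to follow-up; 34 per arm.

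**Step 1: reproduce the 34.**
- Unclustered: n = 2 × ((1.960 + 0.842) / 0.8)² = 24.53 per arm.
- Design effect: 1 + (6 − 1) × 0.07 = 1.35.
- 24.53 × 1.35 = 33.1, rounded up to 34 (no allowance for loss or baseline correlation).
- With the baseline factor 1 − 0.25² = 0.9375 and division by 0.9: 24.53 × 1.35 × 0.9375 / 0.9 = 34.5. Multiplying by 1.1 instead of dividing by 0.9 gives 34.1.
- Without the design effect, the baseline-adjusted version is 24.53 × 0.9375 / 0.9 = 25.5.

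The protocol does not give its formula, but every variant that comes close to 34 needs the design effect. Clustering therefore really is built into the sample size.

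**Step 2: what ignoring it means.** True standard errors are √1.35 = 1.16 times the naive ones, and 34 patients carry the information of 34 / 1.35 ≈ 25. This takes all the correlation to lie at therapy-group level.

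**Step 3: false-positive rate of the three-group ANOVA.** Simulation under no treatment difference, with six groups of six per arm (34 / 6 = 5.7, so about six groups), 40,000 replicates and nominal 5%. The protocol gives no correlation for satisfaction and does not say how much is shared by the parallel groups of a cohort, so both are varied as assumptions.

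| Correlation | All at therapy-group level | Half shared by cohort | All shared by cohort |
|---|---|---|---|
| 0.02 | 6.5% | 5.6% | 4.7% |
| 0.05 | 9.1% | 6.4% | 4.4% |
| **0.07** | **11.0%** | **7.3%** | **4.1%** |
| 0.10 | 14.0% | 8.5% | 3.8% |

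At 0.07 with all the correlation at therapy-group level, an ANOVA on therapy-group means brings the rate back to 4.9%.

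**Step 4: false-positive rate of Fisher's exact test.** Correlation 0.07, all at therapy-group level, same layout. Event rates are assumptions.

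| Event rate | Pairwise | Three-arm |
|---|---|---|
| 3% | 0.4% | 3.6% |
| 5% | 1.2% | 5.8% |
| 10% | 3.3% | 8.8% |
| 20–50% | 5.6–5.9% | 9.8–10.0% |

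Without clustering, the three-arm test runs at 1.1% to 4.4% over these event rates. Pairwise it does not exceed 2.8%. Pairwise, the built-in conservatism of Fisher's test roughly absorbs a correlation of 0.07. With three arms and outcomes that are not rare, it does not.

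**The case against.** Several points against the concern carry weight.

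- **Scope of the Fisher sentence.** It names only adverse events and non-adherence and follows the text on adherence. That it covers reliable change is a fair reading of inclusive wording, since no other test is named for categorical outcomes, but the protocol does not say so.
- **Size for Fisher.** A reader might infer that every P value from these tests is too optimistic. The figures do not support that. Hypotheses 2A and 2E compare CBTi with each comparator, which fits pairwise testing, and pairwise Fisher is close to nominal. The protocol does not say whether the test is pairwise or three-arm.
- **The 7% was set for the sizing outcomes.** No correlation is given for satisfaction, attendance or adverse events. The three groups of a cohort run in parallel, on the same day and in the same place, with the same two therapists (Intervention section). Any correlation from those shared conditions cancels between arms, so 11% is the upper case at 0.07.
- **Intervals.** A reader might infer that the plan's confidence intervals are too narrow. None is stated for these outcomes or for the number needed to treat.
- **Missing data and baseline.** A reader might also infer a complete-case analysis that ignores baseline. The plan provides for multiple imputation, and reliable change is itself a reduction from baseline.

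These points limit size and scope. They leave standing the conflict between the named tests and the clustered design.

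**Conclusion.** The point holds in a limited form. As written, the ANOVA for usefulness and relevance and Fisher's test for categorical outcomes disregard clustering that the protocol assumes elsewhere.

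The ANOVA's error rate is about 4% to 11% at a correlation of 0.07, depending on how much is a shared cohort effect, and this assumes that the 7% carries over to satisfaction. For Fisher's test the problem is material only in three-arm use with outcomes that are not rare. Whether reliable change is affected depends on how the Fisher sentence is read, which the protocol should settle.

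It would go too far to conclude that the trial's main results are compromised. The primary outcomes and the continuous secondary measures are analysed with mixed models, which this point does not touch.

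**What to change.** - **Usefulness and relevance:** use a linear mixed model with therapy group as a random effect, or analyse therapy-group means. If part of the correlation is shared by cohort, an analysis of group means that omits cohort is conservative (3.3% when half is shared at 0.07).
- **Reliable change:** state the method explicitly and use a cluster-adjusted logistic model, either mixed-effects or GEE with a small-sample correction, with therapy group as the cluster. Say whether comparisons are pairwise or three-arm.
- **Number needed to treat:** if an interval is reported, adjust it for clustering.
- **Rare adverse events:** Fisher's test can stay, labelled as descriptive.

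Therapy-group membership is already known, so no new data are needed. The cost is a little more analysis work and somewhat less nominal precision. With only about six groups per arm, a logistic mixed model may be unstable and uncorrected GEE standard errors unreliable, so the small-sample method should be fixed in advance.
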